#### Patient identification and enrollment

**Diagnosis criteria **(Guidelines for Clinical Diagnosis and Treatment of Diabetes in 2008, ADA)

Impaired fasting glucose (IFG) (FPG5.6-6.9 mmol/L) &/or impaired glucose tolerance (IGT) (FPG <5.6 mmol/L & OGTT 2 hPG 7.8-11.1 mmol/L)

**TCM symptoms **(Chinese New Medicine Treatment of Diabetes Clinical Research Guiding Principle)

Dual deficiency of qi and yin or yin deficiency with heat.

##### Inclusion criteria

• Fulfill pre-diabetes diagnostic criteria;

• Fulfill TCM diagnostic criteria;

• Aged 18-75;

• Completed and submitted informed consent form;

##### Exclusion criteria

• History of diabetes (except gestational diabetes);

• Cardiovascular events(cerebrovascular accident in 6 months, history of myocardial infarction or heart failure; severe organic heart disease; aneurysm with the main artery or dissecting aneurysm; specific angina, type II degree atrioventricular block, sick sinus syndrome);

• Impaired hepatic and renal function: AST and/or ALT 2- fold the upper limit of normal or above; same for creatinine. Urine protein > ++ and/or hematuria.

• Fasting triglycerides ≥ 10 mmol/L;

• Endocrine disease, such as hyperthyroidism, autoallergic disease, cancer or other serious fatal illness;

• Former use of glucocorticoid, β receptor blockers, thiazide diuretics and nicotinic acid;

• Pregnancy, preparation of pregnancy and lactating women;

• Suffering from mental diseases or non-cooperation patients;

• Participating in other clinical trial within the last two weeks;

• People refusing to provide consent for the study.

##### Rejection criteria

• Could not take medicine according to the protocol.

• Data is incomplete.

##### Suspension criteria

• Poor compliance.

• Serious adverse events, complications and special physiological changes.

• Unblinded abnormally.

• Reluctance to continue this study.

• Taking medicine forbidding in this study.

• Withdraw for various reasons, such as failure to follow up or death.

• Incomplete information which will influence the study.

• Big mistake in protocol or significant deviation in implement (such as the leak of blind).

• National laws, ministry of science and technology or other authorities decided to terminate the study.

#### Follow up

##### Points of data capture (figure 1)

**Figure 1 F1:**
[figure not shown]
**Points of data capture(unit: month)**.

• Intervention period: 12 months; once a month for 12 months

• After intervention: the 2nd, 6th, 12th month after intervention

##### Contents

Data should be captured according table 1 and 2.

**Table 1 T1:** Content of data capture(to be continued)

Item	Screening period (unit: month)	Intervention period (unit: month)											
	
	-0.5	1	2	3	4	5	6	7	8	9	10	11	12
ICF	X												

Record of medical history	X												

Demographic information	X												

General physical examination	X	X	X	X	X	X	X	X	X	X	X	X	X

FBG	X	X	X	X	X	X	X	X	X	X	X	X	X

PBG	X	X	X	X	X	X	X	X	X	X	X	X	X

OGTT	X	X	X	X	X	X	X	X	X	X	X	X	X

Insulin release test	X												X

HbA1c	X												X

serum TC, LDL-C, VLDL-C	X												X

Blood and urine regulation	X						X						X

ALT, AST	X			X			X			X			X

BUN, Cr	X			X			X			X			X

Electrocardiogram	X												

Pregnancy Test	X						X						X

Selection/exclusion criteria	X												

Drugs of prohibition	X												

SF-36	X												X

Evaluation of TCM Syndrome	X												X

Obtain random code	X												

Dial 800 to Assign drug	X			X			X			X			

Drug Distribution and record	X	X	X	X	X	X	X	X	X	X	X	X	

End-point events		X	X	X	X	X	X	X	X	X	X	X	X

Adverse events	X	X	X	X	X	X	X	X	X	X	X	X	X

Drug combination		X	X	X	X	X	X	X	X	X	X	X	X

X: Item need to be done during different period.

**Table 2 T2:** Content of data capture

Item	Period after intervention (unit: month)		
	
	14	18	24
General physical examination	X	X	X

FBG	X	X	X

PBG	X	X	X

OGTT	X	X	X

Insulin release test			X

HbA1c			X

Serum TC, LDL-C, VLDL-C			X

ECG			X

Blood and urine regulation			X

ALT, AST, BUN			X

SF-36			X

Evaluation of TCM Syndrome			X

Pregnancy test		X	X

End-point events	X	X	X

Adverse events	X	X	X

Drug combination	X	X	X

X: Item need to be done during different period.

#### Outcome measures

##### Index of end point

• Occurrence of type 2 diabetes (according to the guideline of ADA 2008);

• Blood glucose change to be normal.(FPG<5.6 mmol/L & OGTT 2 hPG <7.8 mmol/L)

##### Primary outcomes

• Oral glucose tolerance test

• Insulin releasing test

• Glycosylated hemoglobin (HA1c)

##### Secondary outcome measures

• Score of the Short Form 36 Health Survey Questionnaire(SF-36)

• Scoring of TCM symptom (refer to clinical research guidance of new Investigational drug in TCM)

• Blood lipid: Total Cholesterol (TC), Triglyceride(TG), High Density Lipoprotein-Cholesterol(HDL-C), Low Density Lipoprotein-Cholesterol(LDL-C)

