### Intervention

• Arrangement for intervention: All researchers in this study will be trained before their participation. Some measures will be implemented in order to ensure compliance, such as compensation and prize. Patient handouts will be delivered to every participants to instruct their medication and cooperation.

• Lifestyle intervention: Researchers will develop an individual diet program for each participant, including reasonable match of calories, protein and carbohydrates, low-salt and low-sugar diet, advise them to give up some bad diet habits. Risk factors, such as smoking and alcoholics, will be controlled strictly. Individual's exercise program will be formulated for all participants according to their age, gender, etc.

• Drug intervention: The period of drug intervention is 12 months. All participants have to visit researchers every month. The interventions are as follows: JQJT tablet for treatment group, taking seven tablets each dose and twice daily, all the drugs are taken before meal; Placebo of JQJT for control group, the method and time of taking drugs is the same as treatment group.

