##### Safety index

• General medical examination

• Study visit blood and urine tests

• Functional examination: EKG, ALT, BUN, Cr

• Adverse events.

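### Triglyceride and HDL-C are secondary outcomes but missing from the lipid rows of both visit tables, and ECG, a safety index, has no assessment during or at the end of treatment

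*Protocol article*

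**What the plan says.** The Secondary outcome measures section names the lipid outcomes analyte by analyte: "Blood lipid: Total Cholesterol (TC), Triglyceride(TG), High Density Lipoprotein-Cholesterol(HDL-C), Low Density Lipoprotein-Cholesterol(LDL-C"). The Contents section makes Tables 1 and 2 the instruction for data capture. Each table has one lipid row, and both name the same three analytes: "serum TC, LDL-C, VLDL-C". Table 1 marks that row at screening and month 12, and Table 2 marks it at month 24.

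TG also matters for eligibility. The Exclusion criteria contain "Fasting triglycerides ≥ 10 mmol/L". Table 1 has no TG row at screening, but it does mark a general row for checking selection and exclusion criteria there.

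The Safety index section includes "Functional examination: EKG, ALT, BUN, Cr" and gives no time points. In Table 1 the row "Electrocardiogram" has one mark, at screening. In Table 2 the ECG row has one mark, at month 24. The Intervention section says "The period of drug intervention is 12 months", and the visits that follow are given as "After intervention: the 2nd, 6th, 12th month after intervention", which are months 14, 18 and 24. Creatinine is paired with BUN in Table 1, but the month-24 chemistry row in Table 2 lists ALT, AST and BUN only.

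**The concern.** A site that works from the visit tables would order TC, LDL-C and VLDL-C. It would have no instruction to measure or record HDL-C at all, or TG after baseline. Half of the named lipid outcomes would then be empty, or would depend on what each centre's laboratory happens to report. In a four-city trial that is selective and uncontrolled missingness.

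The plan's missing-data rule does not help. The Analysis of data sets section uses last observation carried forward. HDL-C would have no value to carry. If a screening TG existed, carrying it forward would give every participant a change of zero in both arms by construction.

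For ECG the issue is timing. A safety index for a drug is normally read as describing people who are exposed to it or have just completed it. Here the only post-baseline tracing is taken a year after exposure ends, so a null comparison at month 24 could be mistaken for reassurance about the treatment period.

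**Working it through.** No sample size, power or alpha figure enters this point, and the plan states no figure to reproduce. The check sets the outcome and safety lists against the two visit tables, row by row.

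**Lipids** (outcome list against the lipid rows of Tables 1 and 2)

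| Analyte | Listed outcome | Screening | Month 12 | Month 24 |
|---|---|---|---|---|
| TC | yes | yes | yes | yes |
| LDL-C | yes | yes | yes | yes |
| TG | yes | not listed; implied by the exclusion criterion | no | no |
| HDL-C | yes | no | no | no |
| VLDL-C | no | yes | yes | yes |

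- Outcome-by-visit cells needed: 4 analytes × 3 time points = 12.
- Cells scheduled: 2 analytes × 3 time points = 6.
- Cells not listed: 12 − 6 = 6. If a screening TG is granted because eligibility needs it, 6 − 1 = 5.
- Post-baseline cells (months 12 and 24): 4 × 2 = 8 needed and 2 × 2 = 4 scheduled. All 4 missing cells belong to TG and HDL-C.
- Outcomes with no scheduled post-baseline value: 2 of 4.

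**Safety tests** (Safety index functional list against Tables 1 and 2)

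| Test | Screening | Months 1 to 12 (drug period) | Month 24 |
|---|---|---|---|
| ALT | yes | 3, 6, 9, 12 | yes |
| BUN | yes | 3, 6, 9, 12 | yes |
| Cr | yes | 3, 6, 9, 12 | no |
| ECG | yes | none | yes |

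- ECG during the drug period: 0 of 12 monthly visits, against 4 of 12 for each of ALT, BUN and Cr.
- Time from end of drug to the only post-baseline ECG: 24 − 12 = 12 months.
- ECG is the only one of the four functional tests with no assessment on treatment or at its end.
- Creatinine is covered through the drug period. It is missing only at month 24.

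**Could the mismatch be an artefact?** The lipid row names the same three analytes in both tables, so a single garbled cell is unlikely. Neighbouring rows, such as those for the insulin release test and HbA1c, keep their marks at screening and month 12, so the column positions in Table 1 look sound. Nor is this article condensation, because the article prints both the analyte-level outcome list and the full visit tables, and the two disagree.

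**The case against.** The strongest reply has four parts.

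1. *The row may simply be mislabelled.* The abstract speaks only of a blood lipid test, and a lipid sample is scheduled at three time points. VLDL-C may have been written where HDL-C was meant, with TG dropped. That is plausible, and the document cannot settle it. A reader might infer that the data will certainly be missing, and the text does not support that. It does show that the schedule, followed literally, omits two outcomes. Appealing to a standard panel does not resolve this, because the row names individual analytes. Even on the assumption that a laboratory obtains TG on the way to VLDL-C, nothing requires it to be recorded, and HDL-C would still be absent.

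2. *The exclusion criterion still works.* A reader might infer that the TG criterion cannot be applied. That goes too far, because Table 1 marks an eligibility check at screening, and making that check requires a TG value. What stands is that no TG test is listed there.

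3. *ECG can be evaluated.* A reader might infer that ECG is not collected or cannot be analysed. Neither is right. It is recorded at screening and month 24, so the arms can be compared, and the Safety index section sets no time point that this schedule breaches. What stands is the timing: no information during or at the end of treatment.

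4. *Creatinine at month 24 is trivial.* This largely stands. The safety list does not require creatinine at that visit, and the drug period is covered. It is worth tidying but does not carry the point.

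**Conclusion.** The point holds in a limited form. For lipids there is a printed contradiction between the outcome list and the visit tables. As scheduled, 2 of 4 lipid secondary outcomes have no post-baseline measurement, HDL-C has none at any visit, and VLDL-C is collected without being an outcome. TC and LDL-C are unaffected. For ECG there is a weakness of timing, not an absence of data: 0 of 12 on-drug visits and a single follow-up tracing 12 months after drug stops, so the comparison describes off-drug status.

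The documents do not support saying that all these outcomes cannot be evaluated, or that the TG exclusion cannot be operated.

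The conclusion assumes that sites follow Tables 1 and 2 as printed and that the case report form mirrors them. If the form already carries TG and HDL-C, the lipid part reduces to correcting the tables. The end-point indexes, the primary outcomes and the sample size are not touched, so this is something the sponsor should correct and not a threat to the trial's main conclusion.

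**What to change.** - **Lipids.** Bring the lipid rows of Tables 1 and 2 into line with the outcome list by adding TG and HDL-C at screening, month 12 and month 24. VLDL-C may stay or be dropped. The screening entry also gives the TG exclusion criterion a listed test. The cost is two more assays on blood already drawn: for the 400 randomised participants, at most 400 × 3 × 2 = 2,400 assays, with no extra visit or blood draw. Values not collected at the time cannot be recovered later.
- **ECG.** Reconcile the ECG rows with the safety index so that the comparison can inform on-drug safety, or state plainly that ECG describes only the off-drug follow-up. The second option costs one sentence. The cost of the first depends on how the sponsor reconciles the rows.
- **Creatinine (minor).** Reconcile the month-24 chemistry row with the safety list, either by adding creatinine or by saying that it is assessed only through month 12.
- **Case report form.** Check it against the corrected tables in the same step, so that all three agree.

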##### Safety index

• General medical examination

• Study visit blood and urine tests

• Functional examination: EKG, ALT, BUN, Cr

• Adverse events.

#### Measure and evaluate tools

***Evaluation criteria of efficacy on diabetes conversion rate ***(refer to the guideline of the diagnosis of diabetes mellitus of ADA 2008)

***The rate of blood glucose return to normal ***(refer to the guideline of the diagnosis of diabetes mellitus of ADA 2008)

##### The score of SF-36

Questionnaire is the evaluation of various dimensions, entries, and between groups and within group comparison of questionnaire total score. The score is calculated with measurement data.

***Evaluation of TCM symptom score ***(refer to clinical research guidance of new Investigational drug in TCM)

Quantitative criteria of TCM symptom grades.

#### Adverse Event Monitoring

##### Report of adverse event

When adverse event happens, researchers must fill out the "SAE form" and report it to project office and center ethics committee immediately. The event should also be reported to the safety supervision division of the State Food and Drug Administration within 24 hours.

##### Record of adverse event

Adverse event report form must be filled according to the real circumstances. Some information, including occurrence time, severity, duration, adopted measure of the adverse event should be noted as well.

##### Relationship between adverse event and investigational drugs

Judgment of the relationship between the administration time and adverse reactions; judgment of the relationship between suspected and known adverse reactions of investigational drug; whether suspected adverse reactions disappear or mitigate after discontinuation; whether the same reaction occurred again after taking investigational drug once more.

##### Security evaluation criterion

• Safe without any adverse drug reaction.

• Relative safe with mild adverse drug reactions and unnecessary treatment.

• Having moderate adverse drug reactions and necessary treatment.

• Stopping to take investigational drugs due to adverse reactions.

#### Statistical Analysis Plan

##### Analysis parameters

All parameters will be analyzed by SAS 8.2 software package.

##### Analysis of data sets

• Full analysis set: According to the principle of analysis for intention to treat (ITT), participants will be rejected by smallest and reasonable method. The last observation carried forward (LOCF) method will be used for the missing data supplement.

• Per-protocol set (PPS): PPS should be used in the patients who satisfied with the following characters: compliance is between 80% and 120%; not using prohibited drugs; fit with inclusion criteria; case of completed observation.

• Safety set (SS): All information of safety record will be assessed, including adverse events and laboratory test results.

• Statistical analysis method: Relative risk reduction (RRR), absolute risk reduction (ARR), number needed to treat (NNT) adopt nonparametric methods to evaluate the effectiveness. To adopt t-test, repeated measure analysis of variance, radit test, rank test, survival analysis, Cox proportional hazards regression model and so on.

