### Screening of participants

400 pre-diabetes patients will be divided into the treatment group and the control group (1:1). Participants should be included according to diagnosis criteria and inclusion criteria (reference to the next section).

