### Sample size

According to the results of the "JQJT tablets intervene IGT study" by Professional Committee of Diabetes, Association of Integrative Medicine in Tianjin, annual average tyoe 2 diabetes conversion rate of test group is 4.05%, control group is 12.69%. The sample was estimated according to the parameters: *α *= 0.05, *β *= 0.1

Considering attrition of no more than 20%, the total number of qualified cases in the groups will be 200 each (n = 400).

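### LOCF is fixed for missing data in the full analysis set: it enters zero change for HbA1c and insulin after early loss, and counts unconverted dropouts as non-converters in the binary analysis

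*Protocol article*

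**What the plan says.** Under Analysis of data sets, the full analysis set follows the intention-to-treat principle, and the rule for gaps is: "The last observation carried forward (LOCF) method will be used for the missing data supplement". The article names no other way of handling missing outcomes. The per-protocol set is limited to completed cases, and the dropout analysis only compares dropout between arms.

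The schedule decides what LOCF does to each outcome:

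- **HbA1c and insulin.** In Table 1, the row "Insulin release test" and the HbA1c row are marked only at screening and month 12; Table 2 adds month 24. Both are primary outcomes. The SF-36, the TCM syndrome evaluation and the scheduled lipids follow the same pattern.
- **OGTT and end-point events.** These are marked at every intervention visit ("Intervention period: 12 months; once a month for 12 months") and at months 14, 18 and 24.

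The end points are occurrence of type 2 diabetes and return to normal glucose. The methods listed include chi-square, RRR, ARR and NNT, repeated-measures ANOVA, survival analysis and Cox regression. The article does not say which of the binary or time-to-event methods applies to conversion. The Sample size section gives the planning rates ("conversion rate of test group is 4.05%, control group is 12.69", in per cent) and the dropout allowance ("Considering attrition of no more than 20", in per cent).

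**The concern.** LOCF assumes that a participant's status stays as last seen. For HbA1c and insulin the last value before month 12 is the screening value, so each early loss contributes a change of exactly zero, analysed as if it had been observed. For losses after month 12, the month-12 value stands in at month 24.

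In a binary analysis of conversion, someone lost unconverted at month 2 counts the same as someone followed unconverted to the end. Someone whose last reading was normal counts as reverted.

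The article's own Background describes pre-diabetes as progressing and glucose as rising again after 1-2 years of lifestyle intervention, so stability after dropout is a doubtful assumption. Dropout may also be related to outcome. Use of a forbidden medicine is a suspension criterion, and Bias control forbids drugs with effects similar to the study agent. If suspension ends observation, which the article does not say, a participant who worsens and starts such a drug would keep the earlier, better status.

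Up to 80 of 400 participants (20%) could be affected. The estimates would then depend partly on who left, when, and from which arm, and the standard errors would treat imputed values as observed.

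**Working it through.** **Inputs from the article.** Annual conversion 4.05% (JQJT) and 12.69% (control); 200 per arm; alpha 0.05, power 90%; attrition at most 20%.

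**Assumptions.** The annual rate is the 12-month risk, with constant hazard. Dropout is unrelated to outcome. It is either uniform over the 12 months, with conversions before dropout kept, or all immediately after baseline, as a bound. The article gives no split by arm and no timing.

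**The plan's own sample size.** With unpooled variance and a two-sided test, (1.960 + 1.282)² × (0.0405 × 0.9595 + 0.1269 × 0.8731) / 0.0864² gives 211 per arm, or 264 after dividing by 0.8. The pooled version gives 214 and 268. So 200 is not reproduced this way. The article states neither sidedness nor test, and a one-sided arcsine version comes close (164, then 205). Nothing below depends on how 200 was obtained.

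**Conversion under LOCF.** Expected observed proportion = (1 − d) × p + d × q, where d is the arm's dropout. In the bound q = 0. For uniform dropout q = 1 − p/λ with λ = −ln(1 − p):

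- JQJT: λ = 0.0413, q = 0.0204.
- Control: λ = 0.1357, q = 0.0649.

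For 20% dropout in both arms, uniform timing:

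- JQJT: 0.8 × 0.0405 + 0.2 × 0.0204 = 0.0365.
- Control: 0.8 × 0.1269 + 0.2 × 0.0649 = 0.1145.

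| Dropout JQJT/control | Timing | JQJT % | Control % | ARR, points | RR | NNT |
|---|---|---|---|---|---|---|
| none | – | 4.05 | 12.69 | 8.64 | 0.319 | 11.6 |
| 20%/20% | uniform | 3.65 | 11.45 | 7.80 | 0.319 | 12.8 |
| 20%/20% | bound | 3.24 | 10.15 | 6.91 | 0.319 | 14.5 |
| 30%/10% | uniform | 3.45 | 12.07 | 8.62 | 0.286 | 11.6 |
| 30%/10% | bound | 2.84 | 11.42 | 8.59 | 0.248 | 11.6 |
| 10%/30% | uniform | 3.85 | 10.83 | 6.98 | 0.355 | 14.3 |
| 10%/30% | bound | 3.65 | 8.88 | 5.24 | 0.410 | 19.1 |

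With 200 analysed per arm and a two-sided 5% test, power falls from 88.0% with no dropout to 84.2% with equal 20% uniform dropout.

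**Conversion with no true effect** (12.69% in both arms), dropout 20% JQJT and 5% control:

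- Uniform: 11.45% against 12.38%, a false ARR of 0.9 points and a two-sided type I error of about 5.9%.
- Bound: 10.15% against 12.06%, a false ARR of 1.9 points and a type I error of about 9.3%.

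**HbA1c and insulin at month 12.** If a fraction d of an arm is lost before month 12, its expected mean change is (1 − d) × c, where c is the true change. With d = 0.20 in both arms the difference becomes 0.80 of its true size. With unequal dropout and the same true change c in both arms, the false difference (JQJT minus control) is c × (d_control − d_JQJT). At 20%/5% this is −0.15c, so its direction depends on the sign of c.

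**The case against.** Several stronger readings are tempting, and the documents do not support them.

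- **That every dropout becomes a non-converter.** End-point events are recorded monthly to month 12 and three times afterwards, so a conversion seen before dropout is kept.
- **That baseline is always carried forward.** This holds for HbA1c and insulin after a loss before month 12. Later losses carry month 12 to month 24, and OGTT, measured monthly, normally carries a recent value.
- **That conversion is bound to be analysed with LOCF.** Survival analysis and Cox regression are listed, and conversion is their natural target; dropouts could then be censored. But these methods are assigned to no outcome, while RRR, ARR, NNT and chi-square are named, so the binary analysis remains open.
- **That the listed repeated-measures method avoids the problem.** The article names repeated-measures ANOVA, which in its classical form needs complete rows. It is not a mixed model.
- **That LOCF flatters whichever arm loses more people.** Under uninformative dropout this is so for conversion. For HbA1c and insulin it pulls that arm's mean change towards zero, which hurts an improving arm. For reversion, a participant lost while still pre-diabetic counts as not reverted.

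It is also fair to say that equal, uninformative dropout makes the conversion result conservative, and that the larger distortions need strongly unequal or very early dropout. Nor is the absence of sensitivity analyses from a condensed article a fault in itself, since they may stand in the full plan. What remains is the stated choice of LOCF, which neither the completers' set nor the dropout comparison corrects.

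**Conclusion.** The point holds in this limited form and should be fixed; it does not undermine the trial. LOCF affects two of the three primary outcomes directly, and both end points if they are analysed as binary.

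The relative measure is robust to equal, uninformative dropout. ARR, NNT and mean differences are not: at 20% the ARR loses about 0.8 points with uniform timing, and a month-12 mean difference loses about a fifth. Unequal dropout also moves the RR, from 0.32 to 0.29 (uniform) or 0.25 (bound) at 30%/10%, and to 0.36 or 0.41 at 10%/30%. It can also create a difference where none exists.

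These sizes illustrate assumed splits and timings and are not predictions. Informative dropout, which the figures leave out, could make the bias larger or smaller.

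**What to change.** Replace LOCF as the main method, and settle this before unblinding:

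- **Conversion:** assign the survival/Cox analysis already listed, with censoring at the last glucose assessment. Treat time as grouped or interval-censored, since conversion is detected only at visits.
- **OGTT:** use a likelihood-based mixed model on all observed visits, in place of LOCF with repeated-measures ANOVA.
- **HbA1c and insulin at month 12:** use baseline-adjusted models with multiple imputation.
- **Sensitivity:** add one analysis that gives dropouts an unfavourable risk, for example that of the placebo arm.
- **LOCF:** keep it only as a supportive analysis.

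The cost is plan wording and programming, with no new data, because the monthly OGTT and end-point records are already scheduled. The new main methods assume that data are missing at random (for the survival analysis, that censoring is uninformative). The sensitivity analysis is there to probe that assumption.
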